**Figure 2 F2:**
[figure not shown]
Study components of the control and the intervention (RESST) group. CR, cardiac rehabilitation; RESST, REfining Sleep and STress.

The intervention was developed at Capri Cardiac Rehabilitation and is based on principles from Acceptance and Commitment Therapy (ACT) and ACT for insomnia (ACT-i), where the observation and acceptance of thoughts, emotions and physical experiences is a central concept, while committing to value-based actions.^37^ Additionally, elements of CBT-i are incorporated, including psychoeducation on sleep and its underlying physical processes, sleeping conditions and stress reduction.

The RESST intervention takes a comprehensive approach (table 1) to address sleep-related difficulties and stress management, incorporating the following elements:

Psychoeducation: Participants receive education about the physiological aspects of sleep and the interplay between sleep, stress management and overall well-being and health. They learn about the importance of sleep hygiene (including stimulus control, and if necessary: sleep restriction) and stress reduction in promoting better sleep and (mental) health.Mindfulness and cognitive defusion: Mindfulness exercises are practised, cultivating awareness of present-moment experiences. Participants learn to observe and accept thoughts, emotions and physical sensations related to sleep and stress without becoming entangled in them. They are guided to observe their thoughts without automatically reacting to them. By developing awareness of unhelpful thoughts and deeply ingrained beliefs and creating distance from them, individuals can reduce their impact on emotions and behaviours.Acceptance and self-compassion: Participants learn to make space for inner discomfort (difficult thoughts, negative emotions and unpleasant physical sensations), without having to change them or be limited by them. They gain insight into self-imposed pressure and develop a kind, supportive attitude towards themselves.Values clarification and committed action: Through guided exercises within and between sessions, participants identify their personal values and goals related to sleep, stress management and overall health. This process aids them in aligning their behaviours with their values and establishing a sense of purpose in making positive changes.

**Table 1 T1:** Components of the RESST intervention

Session	Topics discussed
Week 1	Biological mechanisms and functions of stress; Effects of long-term stress; Interaction between sleep and stress; Recognising stress signals and behaviours;
Week 2	Biological mechanisms and functions of sleep; Sleep hygiene and lifestyle factors; Insight into own sleeping habits; Insights in thoughts in daily situations;
Week 3	Recognising own patterns around sleep; Role of thoughts when tense; Observing thoughts; Behaviour when lying awake;
Week 4	Recognising own thought patterns; Time-outs for recognising stress signals; Mindfulness; Role of thoughts in coping with stress; Making healthier decisions in daily life regarding stress and relaxation; Acceptance; Letting go of built-up tension; Cognitive defusion;
Week 5	Value clarification and committed action; Making healthier decisions in daily life regarding stress and relaxation; Mindfulness; Recognising physical tension and letting go; Acceptance; Self-compassion.

RESST, REfining Sleep and STress.

Between each session, participants receive handouts with information and exercises to reflect on their own behaviour patterns and practice their skills between sessions.

### Outcome assessment

Baseline characteristics and measurements are collected at the start of the CR programme, 3 months later (post-CR) and a final assessment is performed 6 months after the start of CR (figure 3). An overview of all outcomes, manner and timing of assessment is shown in table 2. Below, we elaborate on the primary and secondary outcomes and their manner of assessment.

**Figure 3 F3:**
[figure not shown]
Timeline of the study showing follow-up duration and timing of the measurements (physical examination, questionnaires, accelerometer, EMA). EMA, ecological momentary assessment; RESST, REfining Sleep and STress.

**Table 2 T2:** Outcomes, manner of assessment and timing of assessment

Outcome	Measurement tool	Assessment
Primary outcomes		
Accelerometry-assessed sleep (sleep duration, sleep latency, wake-after-sleep-onset and sleep efficiency)	GENEActiv accelerometer (Activinsights, Kimbolton, UK)	T0, T3m, T6m
Self-reported sleep quality	Pittsburgh Sleep Quality Index^32^	T0, T3m, T6m
Perceived stress level	Perceived Stress Scale-10^41^	T0, T3m, T6m
Secondary outcomes		
Cardiometabolic risk factors		
Biomarkers of chronic stress: hair cortisol and cortisone	Liquid chromatography-tandem mass spectrometer (Waters, Manchester, UK)	T0, T3m, T6m
Body mass index	Stadiometer, weighing scale	T0, T3m, T6m
Blood pressure	Automatic sphygmomanometer (Omron X2 Basic)	T0, T3m, T6m
Smoking behaviour	Carbon monoxide breath tester (piCO Smokerlyzer, Bedfont Scientific, Maidstone, UK) and self-designed questionnaire	T0, T3m, T6m
Physical fitness (hand-grip strength)	Hand-held dynamometer (Jamar)	T0, T3m, T6m
Physical activity and sedentary behaviour	GENEActiv accelerometer	T0, T3m, T6m
Estimated cardiorespiratory fitness	FitMáx-Questionnaire^63^	T0, T3m, T6m
Alcohol use	Five Shot questionnaire^64^	T0, T3m, T6m
Psychosocial measures		
Health-related quality of life	MacNew^65^	T0, T3m, T6m
Fatigue	Fatigue Severity Scale^66^	T0, T3m, T6m
Anxiety and depression	Hospital Anxiety and Depression Scale^67^	T0, T3m, T6m
Participation in society	Utrechtse Schaal voor Evaluatie van Revalidatie-Participatie^68^	T0, T3m, T6m
Sleep and stress disorders		
Presence of restless legs syndrome	Restless Leg Syndrome Rating Scale^69^	T0
Presence of insomnia	Insomnia Severity Index^70^	T0
Risk of presence of obstructive sleep apnoea	STOP-Bang questionnaire^71^	T0
Diagnosis of sleep disorders	EHR and anamneses	T0
Prior treatment for sleep disorders	EHR and anamneses	T0
Prior treatment for stress management	EHR and anamneses	T0
Cost-effectiveness and implementation parameters		
Costs incurred by patients	iMTA Medical Consumption Questionnaire,^72^ iMTA Productivity Costs Questionnaire,^73^ EHR, costs from the intervention	T3m, T6m
Health utility score	EuroQol 5D-5L (EQ-5D-5L)^74^	T0, T3m, T6m
Satisfaction RESST intervention	Self-designed questionnaire	T3m
Facilitators and enablers of the intervention	Semi-structured interviews with patients and healthcare professionals	Post-intervention
Momentary measures		
Perceived sleep	Electronic diary: Consensus Sleep Diary (CSD)^46^	T0, T3m, T6m
Diet	Electronic diary: Intake of caffeine and alcohol, timing of the main meal (self-designed)	T0, T3m, T6m
Momentary fatigue	Electronic diary: self-designed questions	T0, T3m, T6m
Momentary stress	Electronic diary: self-designed questions	T0, T3m, T6m
Adherence		
Adherence to CR treatment	EHR	T3m
Adherence to the RESST intervention	EHR	T3m
Baseline characteristics		
Sex	Single-item question	T0
Age	EHR	T0
Cardiac diagnosis	EHR	T0
(Changes in) Medication use	EHR	T0, T3m, T6m
Drug use	Self-designed questionnaire	T0
Socioeconomic status	Neighbourhood socioeconomic status determined via postal code (EHR)	T0
Country of origin	Single item question	T0
Country of origin of parents	2-item question	T0
Employment status and presence of irregular or night shifts	2-item question	T0
Marital status	Single-item question	T0
Educational level	Single-item question	T0

CR, Cardiac rehabilitation; EHR, electronic health record; RESST, REfining Sleep and STress; T0, baseline assessment; T3m, 3-month assessment; T6m, 6-month assessment.

#### Primary outcomes

The primary outcomes are both accelerometer-assessed and self-reported sleep, and perceived psychological stress. Sleep is objectively assessed using the GENEActiv accelerometer, which is worn on the non-dominant wrist for 7 consecutive days and nights. The GENEActiv is a tri-axial, wrist-worn accelerometer, which has shown good agreement for sleep-related parameters with gold-standard polysomnography.^38^ With validated algorithms (GGIR package in R), sleep duration, sleep latency, wake-after-sleep-onset and sleep efficiency are estimated. Sleep latency is the time it takes to fall asleep, wake-after-sleep-onset is the time spent awake between the first time falling asleep and the last time waking up, and sleep efficiency is the percentage of time spent asleep between the first time falling asleep and last awakening. Additionally, sleep quality is self-reported with the PSQI.^32^ The PSQI is a widely used tool to measure sleep quality, also in cardiac populations, and was shown to be valid in both clinical and non-clinical samples.^39 40^ Psychological stress is measured with the PSS-10, which was shown to be valid for assessing perceived stress.^41 42^

#### Secondary outcomes

Secondary outcomes include cardiometabolic risk factors, including physical behaviour, biomarkers of chronic stress, blood pressure, body mass index, physical fitness and smoking behaviour. Physical behaviour, comprising physical activity and sedentary behaviour, is assessed using the GENEActiv accelerometer. Using a liquid chromatography-tandem mass spectrometer, biomarkers for chronic stress (cortisol and cortisone) are determined from the most proximal centimetre of a scalp hair sample. During each study visit, blood pressure is measured twice in a sitting position using an automatic sphygmomanometer and averaged. Height and weight are measured without shoes and with heavy garments or items removed. Hand-grip strength, a measure of physical fitness, is assessed using a hand-held dynamometer. Smoking behaviour is tested with a carbon monoxide breathalyser.

Questionnaires are used to assess psychosocial outcomes, the possible presence of sleep disorders, including the risk of having obstructive sleep apnoea, alcohol and smoking behaviour, treatment satisfaction in the intervention group, QoL, and intervention, medical and productivity costs incurred for the cost-effectiveness analysis (table 2). Semistructured interviews with patients and their relatives, as well as healthcare providers, will be conducted to gather information on enablers and barriers of the RESST intervention.

Momentary outcomes are assessed using smartphone-based ecological momentary assessment (EMA) during the 7 days the accelerometer is worn, via the MovisensXS app (Movisens, Karlsruhe, Germany). The measurement of momentary fatigue consists of three questions asking for feelings of tiredness, fitness and physical exhaustion and is based on the Short Fatigue Questionnaire.^43^ Momentary stress is also assessed with three questions, including two items from the PSS-10 questionnaire and one emotion item on nervous or stressed feelings. The questions were adapted for momentary use and previously used in EMA studies investigating momentary perceived stress.^44 45^ Prompts for momentary fatigue and momentary stress are sent six times per day, between 09:00 and 21:00 hours at random configuration, with at least 1 hour between prompts. The MovisensXS software is also used to prompt caffeine intake at 12:00 hours, 17:00 hours and 21:00 hours. Furthermore, a prompt is sent for alcohol use and timing of the main meal of the previous day using a start-of-day questionnaire. Furthermore, a sleep diary (Consensus Sleep Diary) is kept via the start-of-day questionnaire.^46^

Baseline characteristics regarding personal, disease-related and demographic measures are obtained from electronic health records and self-designed questionnaires. Attendance to the CR sessions and attendance to the intervention sessions are retrieved from electronic health records. A self-designed questionnaire is administered by a nurse via telephone to assess possible (serious) adverse events and other hospital visits.

Due to the nature of the study, blinding of participants and those giving the intervention is not possible. To minimise bias, objective measures of sleep and stress are also obtained using the GENEActiv accelerometer, as well as hair cortisol and cortisone.

### Sample size

The chosen sample size was based on expected differences in three somewhat related primary endpoints. We aim to detect an effect on at least one of these endpoints with a power of 80%. Therefore, for each comparison, a two-sided alpha of 0.017 was used.

Regarding sleep duration, the estimated mean±SD at 3-month measurement is 6.2±0.9 hours for the control group.^47^ We hypothesised that this value would be 10% higher for patients randomised to CR+RESST, equating to 6.8±0.9 hours at 3-month measurement. To detect this mean difference of 0.6 hours, 49 participants per group are needed. Regarding sleep quality, the expected mean PSQI score is 6.5±2.6 at 3-month follow-up for the control group, and 4.4±2.6 for the intervention group, based on research by Ghane *et al* and unpublished data from the OPTICARE-XL trial.^48^ To detect this mean difference in PSQI of 2.1 points between the control and intervention group, 68 participants are required. For the last primary outcome, perceived psychological stress, we expect a mean PSS-10 score of 15.4±8.2 is expected after CR alone, and a mean score of 11.1±8.2 for the intervention group.^19^ To detect this mean difference of 4.3 points, 156 participants are required. Thus, accounting for a minimum of 156 participants and a dropout of approximately 25%,^49 50^ we plan to include 200 participants in the study. This sample size will also allow us to take a number of covariates into account which may be associated with intervention effectiveness.

Drop-out and adherence will be continuously monitored throughout the study. If both remain lower than expected, participant inclusion may be stopped before reaching 200 participants to prevent unnecessary burdening.

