During the project, end-users, such as patients, health practitioners and policy makers—including guideline developers and healthcare insurers—will be actively involved to develop a roadmap for further optimisation and implementation of the RESST intervention. Barriers and enablers, as well as participants’ perceptions and satisfaction, will be assessed. These barriers and enablers will inform the selection of implementation strategies, using the Expert Recommendation for Implementation Change taxonomy.^62^ This approach will maximise the real-world impact of the intervention and increase the likelihood of successful implementation if the intervention proves effective and cost-effective. If the intervention is not proven effective, the obtained insights will be essential to understand how the intervention can be improved to better meet patients’ needs.

In conclusion, we hypothesise that integrating a tailor-made behavioural intervention targeting sleep and stress into CR will significantly improve both outcomes. This is highly relevant given that over half of cardiac patients experience sleep and/or stress complaints, which negatively impact cardiovascular recovery and health, increase hospital readmissions and reduce QoL. If effective, this intervention has strong potential for implementation, offering a scalable solution to enhance patient recovery and long-term well-being.

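### The sample-size section states 80% power for at least one endpoint, but the calculation gives 80% for each endpoint separately; the sample size itself stands

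*Protocol article*

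**What the plan says.** The Sample size section opens: "The chosen sample size was based on expected differences in three somewhat related primary endpoints". It then gives the power target, "We aim to detect an effect on at least one of these endpoints with a power of 80" (per cent), and draws the test level from it: "Therefore, for each comparison, a two-sided alpha of 0.017 was used".

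Each endpoint is then sized in turn:

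- **Sleep duration:** "the estimated mean±SD at 3-month measurement is 6.2±0.9 hours for the control group", with 6.8 hours expected under the intervention. "To detect this mean difference of 0.6 hours, 49 participants per group are needed".
- **PSQI:** "the expected mean PSQI score is 6.5±2.6 at 3-month follow-up for the control group, and 4.4±2.6 for the intervention group". "To detect this mean difference in PSQI of 2.1 points between the control and intervention group, 68 participants are required".
- **PSS-10:** expected means 15.4 and 11.1, SD 8.2 in both groups, a difference of 4.3 points, 156 participants.

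The section treats 156 as the minimum, allows for dropout of about 25% and arrives at 200. It also lets inclusion stop short of 200 if dropout and adherence turn out lower than expected.

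The Statistical analysis section names linear mixed models for the change from baseline to 3 months as the primary analysis and gives no multiplicity procedure. Table 2 and the Primary outcomes section list four accelerometer sleep parameters, plus PSQI and PSS-10, as primary.

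**The concern.** Power for at least one of three endpoints and power for each of three endpoints are different quantities. The section states the first and computes the second.

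This matters in two ways. First, 156 serves as the floor when deciding whether inclusion may end before 200. On the stated target, 156 is far more than needed, so falling below it would look harmless. On the actual calculation, it is the point at which PSS-10 power reaches 80%. Second, 0.017 per comparison is the only multiplicity provision in the article. If it were also used as a fixed test level, PSS-10, the endpoint with least power, would forgo some power that a step-down procedure with the same family-wise error can recover.

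**Working it through.** **Inputs.** From the Sample size section: differences and SDs of 0.6 and 0.9 h (sleep duration), 2.1 and 2.6 (PSQI), 4.3 and 8.2 (PSS-10); two-sided alpha 0.017; power 0.80. From the Design section: 1:1 allocation. The correlation between endpoints is not given, so a common correlation between 0 and 0.8 is assumed.

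**Step 1: reproduce the plan's figures.** Two-sample t-test (noncentral t), with standardised effect d = difference / SD.

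| Endpoint | d | n per arm for 80% | Rounded | Plan |
|---|---|---|---|---|
| Sleep duration | 0.6/0.9 = 0.667 | 48.35 | 49 per arm | 49 per group |
| PSQI | 2.1/2.6 = 0.808 | 33.41 | 34 per arm, 68 total | 68 |
| PSS-10 | 4.3/8.2 = 0.524 | 77.24 | 78 per arm, 156 total | 156 |

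All three match exactly, so each is a single-endpoint calculation.

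**Step 2: power of each endpoint at 78 per arm.** Normal approximation: power ≈ Φ(d√(n/2) − z), with z = 2.387 for two-sided 0.017 and √(78/2) = 6.245.

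- Sleep duration: 0.667 × 6.245 = 4.163, power 96.2%
- PSQI: 0.808 × 6.245 = 5.044, power 99.6%
- PSS-10: 0.524 × 6.245 = 3.275, power 81.3% (80.5% by t-test)

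**Step 3: power for at least one endpoint at 156.** With independent endpoints this is 1 − (1 − 0.962)(1 − 0.996)(1 − 0.813), which exceeds 99.9%. Simulation of correlated normal test statistics gives 99.95% at correlation 0.3, 99.9% at 0.5 and 99.7% at 0.8. None is near 80%.

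**Step 4: size that would match the stated target.** With independent endpoints and 20 per arm, the single-endpoint powers are 39.0%, 56.7% and 23.3%, and 1 − 0.610 × 0.433 × 0.767 ≈ 0.80. At correlation 0.3 about 24 per arm are needed (80.8%), and at 0.8 about 30 (79.7%). That is about 40 to 60 in total, not 156.

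**Step 5: when the sentence would be right.** If only PSS-10 has a true effect, at-least-one power at 156 with independent endpoints is 1 − (1 − 0.813) × 0.983² = 0.819, and about 82% for correlations up to 0.5. That is not the planning scenario, which assumes effects on all three.

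**Step 6: the floor.** 200 less 25% is 150, or 75 per arm. PSS-10 power is then 79% by t-test (79.5% by normal approximation), just under 80%.

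**Step 7: what Holm would add.** Holm compares the ordered p-values with 0.05/3, 0.05/2 and 0.05. Normal approximation, simulated:

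| Scenario | PSS-10 at 0.017 | PSS-10 with Holm | Gain |
|---|---|---|---|
| 156 analysed, all effects as planned | 81.3% | 90.1–90.4% | about 9 points |
| 150 analysed, all effects as planned | 79.5% | 89.0–89.2% | about 10 points |
| 200 analysed, all effects as planned | 90.7% | 96% | about 5 points |
| 156, both sleep effects halved | 81.3% | 83.4–85.4% | 2 to 4 points |
| 156, no sleep-duration effect | 81.3% | about 85% | about 4 points |
| 156, no effect on either sleep endpoint | 81.3% | 81.3% | none |

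With all effects as planned at 156, power to reject all three rises from 77.9–80.8% to 89.1–90.2%.

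**The case against.** The strongest reply is that nothing is broken. The sample sizes are correct, sizing on the hardest endpoint exceeds the stated aim, and no test or estimate changes. The sentence can also be read generously: the at-least-one aim explains why alpha is split, and 80% is the lowest power the trial would have if only one endpoint, whichever it is, were truly affected. It stands that the error is conservative and confined to wording. But the text does not state that worst-case reading, and it conflicts with the planning assumption of three simultaneous effects.

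Two stronger readings are tempting and should not be adopted.

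- **That the trial will test PSS-10 at a needlessly strict fixed level.** The article uses 0.017 for sizing. The Statistical analysis section fixes no multiplicity procedure, and the analysis plan, which is not shown, may already provide one. Bonferroni testing would in any case be valid. Holm is therefore an optional improvement, not the repair of an error, and its gain depends on the sleep effects.
- **That success is defined as improvement in both sleep and stress, so that an at-least-one target undercuts the trial's claim.** The Discussion does expect that an intervention "targeting sleep and stress into CR will significantly improve both outcomes", but it says so as a hypothesis. No section makes it a success criterion, and none says that a sleep-only result would be reported as a combined effect.

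**Conclusion.** The stated power property is wrong for the calculation given. The 156 is the number needed for 80% power on PSS-10 alone at two-sided 0.017, and it gives at least 80% for each of the three endpoints. Under the protocol's effects, power for at least one endpoint is over 99%. The sample size is correct for its inputs and need not change. The practical consequence is limited to what the 156 floor is understood to protect.

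These results assume the protocol's effects and SDs, two-sample comparisons at 3 months and a common correlation of 0 to 0.8. The Holm gain of about 9 points further assumes that both sleep effects are as large as planned and that 156 are analysed.

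**What to change.** **Restate the target.** Replace the at-least-one sentence with: 156 analysed participants give at least 80% power for each of sleep duration, PSQI and PSS-10 separately at two-sided alpha 0.017. Add that PSS-10 sets this floor and that at 150 analysed its power is about 79%. This costs one or two sentences and no patients.

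**Optional.** Name sleep duration at 3 months as the single accelerometer endpoint in the confirmatory family; this comes first, because four accelerometer parameters are now listed as primary. Then test the three endpoints with Holm at overall two-sided 0.05 and report claims per endpoint. Holm never rejects less than Bonferroni at 0.05/3 and controls the same family-wise error. The cost is wording in the protocol and analysis plan, and simultaneous confidence intervals that are less simple than under Bonferroni. If unadjusted 95% intervals are shown beside Holm-adjusted p-values, say so, since the two can disagree.

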The statistical analyses will not be blinded due to limited study resources. However, the data analysis plan will be discussed with a biostatistician prior to conducting the analyses, and code will be checked by an independent researcher to prevent bias. Additionally, data and code will be made available in a data repository after study termination to promote transparency.

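### Alpha is split over three primary endpoints, but six variables are listed as primary; if all six count, the family-wise error exceeds 5%

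*Protocol article*

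**What the plan says.** The Sample size section counts three endpoints: "The chosen sample size was based on expected differences in three somewhat related primary endpoints". It states the aim as "We aim to detect an effect on at least one of these endpoints with a power of 80" per cent, and draws the significance level from that aim: "Therefore, for each comparison, a two-sided alpha of 0.017 was used". It then gives a calculation for sleep duration, one for PSQI and one for PSS-10, and for nothing else.

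Table 2, under its primary heading, has three rows. One of them reads "Accelerometry-assessed sleep (sleep duration, sleep latency, wake-after-sleep-onset and sleep efficiency"; the other two are PSQI and PSS-10. The Primary outcomes text repeats the four accelerometer variables ("sleep duration, sleep latency, wake-after-sleep-onset and sleep efficiency are estimated"), then adds PSQI ("Additionally, sleep quality is self-reported with the PSQI") and PSS-10. Neither place says which accelerometer variable carries the primary test, and neither gives a composite or a joint rule.

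The Statistical analysis section applies linear mixed models to primary and secondary endpoints alike. The change from baseline to 3 months is the primary analysis and the 6-month change is exploratory. It does not reduce the list.

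**The concern.** A level of 0.017 per test holds the chance of at least one false positive near 5% only when there are three tests. Six variables carry the primary label. A reader who takes Table 2 at face value would test six, and the level was not chosen for that.

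What is at stake is the meaning of a positive trial. Participants and providers cannot be blinded, so the accelerometer outcome is the objective counterpart to the two questionnaires. If it may succeed on any of four variables, it has more chances than either questionnaire, and the split makes no allowance for them. A report that claims success on, say, sleep latency alone could be defended from Table 2 and rejected from the Sample size section.

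**Working it through.** **Inputs.** From Sample size: two-sided level 0.017; power 80%; sleep duration difference 0.6 h, SD 0.9; PSQI 6.5 against 4.4, SD 2.6; PSS-10 15.4 against 11.1, SD 8.2; stated needs of 49 per group, 68 in total and 156 in total. From Design: 1:1 allocation. From Table 2 and Primary outcomes: the list of primary variables. The article gives no correlations between them, so every correlation below is an assumption.

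**1. Reproduce the plan's figures.** 0.05/3 = 0.0167, rounded to 0.017. Standardised differences are 0.6/0.9 = 0.67, 2.1/2.6 = 0.81 and 4.3/8.2 = 0.52. A two-sample t-test at 0.017 and 80% power needs:
- sleep duration: 48.35, so 49 per group (stated: 49)
- PSQI: 33.41, so 34 per group, 68 in total (stated: 68)
- PSS-10: 77.24, so 78 per group, 156 in total (stated: 156)

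All three agree. With no split (0.05) the totals would be 74, 52 and 118; with a split by six (0.05/6 = 0.0083) they would be 114, 78 and 180. Of these three options, only the split by three gives the stated numbers.

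**2. Count the listed variables.** Four accelerometer variables + PSQI + PSS-10 = 6. The 6-month comparison is exploratory, so it adds no primary test.

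**3. Family-wise error, independent tests.** The formula is 1 − (1 − α)^k, with Bonferroni bound k × α.
- k = 3: 1 − 0.983³ = 5.0%; bound 3 × 0.017 = 5.1%
- k = 6: 1 − 0.983⁶ = 9.8%; bound 6 × 0.017 = 10.2%

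**4. Family-wise error, correlated tests** (simulated two-sided z-tests at 0.017, 2 million draws, one common correlation for all pairs):

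| Correlation | Six tests | Three tests |
|---|---|---|
| 0.3 | 9.1% | 4.9% |
| 0.5 | 8.0% | 4.5% |
| 0.7 | 6.4% | 4.0% |
| 0.8 | 5.3% | 3.6% |

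**5. Allow for overlap between the sleep variables.** The article says that "sleep efficiency is the percentage of time spent asleep between the first time falling asleep and last awakening". Efficiency so defined must move closely with wake-after-sleep-onset (WASO). Setting the WASO–efficiency correlation at 0.80 to 0.95 in size and the other pairs at 0.1 to 0.6 gives 7.3% to 8.8%. In the extreme case where efficiency merely duplicates WASO, five distinct tests remain: 1 − 0.983⁵ = 8.2% if independent, 7.7% at correlation 0.3 and 6.9% at 0.5.

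**6. Cost of keeping all six.** At 0.0083 per test, PSS-10 needs 180 evaluable participants instead of 156. With 156 evaluable, its power falls from 80% to 73%. Having 180 evaluable out of 200 leaves room for (200 − 180)/200 = 10% dropout, against the roughly 25% that the plan expects.

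**The case against.** The strongest reply is that the at-least-one aim refers to the three endpoints that the same section goes on to size. Table 2 has three primary rows, with the four accelerometer variables in brackets inside one row, and the Primary outcomes text says only that these are estimated. Three rows and a split by three agree. Nowhere does the article say that latency, WASO or efficiency will be tested at 0.017, or that a win on one of them makes the trial positive. This stands. A reader might infer that the trial's family-wise error simply is 8–10%; the article does not support that as a fact. It is a consequence of one reading.

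A reader might also infer from "The statistical analyses will not be blinded due to limited study resources" that the favourable accelerometer variable will be chosen afterwards. The article does not support that either. The same paragraph has the analysis plan discussed with a biostatistician before the analyses, the code checked by an independent researcher, and data and code made available. These steps do not settle which variable decides, but they weigh against reading the sentence as an opening for selection.

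The 10% end is the least plausible, because the sleep variables overlap. It would go too far, however, to call efficiency an exact function of duration and WASO: sleep duration is not defined in the article, and a 7-night mean of ratios is not the ratio of the means.

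Finally, an unseen analysis plan may name one variable. That does not remove the point. Choosing sleep duration there would leave Table 2 and the Primary outcomes text listing three further variables as primary, and keeping six would contradict the Sample size section.

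**Conclusion.** The point holds as a conflict within the article, with an inflation that depends on how the conflict is resolved. The split by three is correct for the three sized endpoints and reproduces exactly.

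- If all six listed variables are tested at 0.017 and any one counts as success, the family-wise error is about 6–9% under plausible correlations, 9.8% under independence and at most 10.2%. It comes down to near 5% only if all six correlate at about 0.8.
- If sleep duration alone is the accelerometer primary endpoint, the error is about 5%, and the primary list in Table 2 and the Primary outcomes text is what needs correcting.

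Either way the wording has to change, because it decides what counts as a positive result. The correlations are assumed; the count of six against three is in the text.

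**What to change.** Name accelerometer sleep duration, the variable on which the trial was sized, as the single accelerometer primary endpoint. Move sleep efficiency, sleep latency and WASO to the secondary outcomes in Table 2 and in the Primary outcomes text. State in the Statistical analysis section that the three primary tests of change from baseline to 3 months are each judged at two-sided 0.017 (or exactly 0.05/3), or by Holm at overall 0.05. Settle this before any comparison by arm.

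The cost is wording, with the same change carried into the analysis plan and registry entry where they list these outcomes. Three variables lose primary status. No participants or measurements are added, and the sample size stands. Masked analysis is not needed to settle this point. Keeping all six as primary is possible only with a procedure that covers all six and a recalculated sample size, which is the dearer route.
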